## Abstract

**Background:**

Ventilator-associated pneumonia (VAP) is the most common infection in intubated critically ill patients. Microaspiration of the contaminated gastric and oropharyngeal secretions is the main mechanism involved in the pathophysiology of VAP. Tracheal cuff plays an important role in stopping the progression of contaminated secretions into the lower respiratory tract. Previous in vitro studies suggested that conical cuff shape might be helpful in improving tracheal sealing. However, clinical studies found conflicting results. The aim of this study is to determine the impact of conical tracheal cuff shape on the microaspiration of gastric contents in critically ill patients.

**Methods/Design:**

This prospective cluster randomized controlled crossover open-label trial is currently being conducted in ten French intensive care units (ICUs). Patients are allocated to intubation with a polyvinyl chloride (PVC) standard (barrel)-shaped or a PVC conical-shaped tracheal tube. The primary objective is to determine the impact of the conical shaped tracheal cuff on abundant microaspiration of gastric contents. Secondary outcomes include the incidence of microaspiration of oropharyngeal secretions, tracheobronchial colonization, VAP and ventilator-associated events. Abundant microaspiration is defined as the presence of pepsin at significant level (>200 ng/ml) in at least 30 % of the tracheal aspirates. Pepsin and amylase are quantitatively measured in all tracheal aspirates during the 48 h following inclusion. Quantitative tracheal aspirate culture is performed at inclusion and twice weekly. We plan to recruit 312 patients in the participating ICUs.

**Discussion:**

BEST Cuff is the first randomized controlled study evaluating the impact of PVC tracheal-cuff shape on gastric microaspirations in patients receiving invasive mechanical ventilation. Enrollment began in June 2014 and is expected to end in October 2015.

**Trial registration:**

ClinicalTrials.gov Identifier: NCT01948635 (registered 31 August 2013).

## Background

### Ventilator-associated pneumonia as a common intensive care unit-acquired infection

Ventilator-associated pneumonia (VAP) is the most common ICU-acquired infection in intubated critically ill patients [1, 2]. VAP is associated with prolonged duration of mechanical ventilation, and ICU stay, increased antibiotic use, mortality and additional cost [3–6]. During the last decades, VAP prevention has become a major quality-indicator in ICU patients [7, 8].

### Microaspiration and pathogenesis of ventilator-associated pneumonia

Microaspiration of gastric and oropharyngeal contaminated secretions represents the primary mechanism of VAP pathogenesis [9–11]. Whereas microaspiration of contaminated secretions is common in intubated critically ill patients, many of them do not develop subsequent VAP. Local and general defense mechanisms frequently prevent the progression from tracheobronchial colonization to ventilator-associated tracheobronchitis, and VAP. However, when these mechanisms are insufficient and/or when quantity and/or virulence of aspirated microorganisms are high, lower respiratory tract infections develop in critically ill patients [9].

Many risk factors for microaspiration have been identified and could be classified into those related to a tracheal tube, to mechanical ventilation, to enteral nutrition, and to the patient. Impossible closure of the vocal cords, longitudinal folds in the PVC-cuffed tracheal tube, and underinflation of the tracheal cuff under 20 cmH_2_O are the main factors related to the tracheal tube. Zero positive end-expiratory pressure, low peak inspiratory pressure, and tracheal suctioning are those related to mechanical ventilation. Enteral feeding and nasogastric tubes are also important risk factors for microaspiration because they are associated with gastroesophageal reflux, gastric distension, and loss of the anatomic integrity of the lower esophageal sphincter. Patient-related risk factors are supine position, sedation and paralytic agents use, hyperglycemia, viscosity of the oropharyngeal secretions above the cuff, tracheal diameter, and tracheal tube mobilization [9].

Pepsin derives from pepsinogen and is released from the chief cells in the stomach [12]. Many animal and human studies have suggested that its presence in tracheal secretions reflects gastric microaspiration in intubated subjects [13–16]. Using pepsin as a marker of gastric microaspiration in intubated critically ill patients is easy to perform routinely. Benefits in using this quantitative biomarker are that it is a noninvasive procedure and that it offers the possibility to quantify microaspiration. Using a quantitative marker to diagnose microaspiration is important because VAP occurrence is closely correlated to the amount of aspirated microorganisms [17, 18].

Evaluating the impact of preventive measures on microaspiration of gastric contents is an interesting strategy because microaspiration is more common than VAP. Therefore, before performing large studies aiming to determine the impact of a preventive measure on VAP incidence, a study evaluating the impact of such a measure on the incidence of microaspiration would probably be helpful to confirm its efficiency.

### Conical cuff shape and ventilator-associated pneumonia

Tracheal cuff shape seems to play an important role in preventing microaspiration and VAP. A conical (tapered)-shaped tracheal cuff insures a permanent sealing zone between the external cuff diameter and the internal trachea diameter, whatever the size and the diameter of the trachea. This permanent contact between the cuff and the trachea would prevent longitudinal folds and reduce microaspiration [19].

Three in vitro studies have examined the relation between conical cuff shape and fluid or air leakage [20–22]. Dave et al. demonstrated that there was no significant difference between a polyurethane conical versus a cylindrical cuff on fluid leakage around the cuff when tracheal diameter is small [20]. In contrast, conical shape was more effective than cylindrical shape for reducing fluid leakage in large-diameter tracheas. In another study, Zanella et al. did not find any significant difference in fluid leakage between polyurethane conical versus cylindrical cuffs [22]. Madjpour et al. reported that conical-shaped PVC cuffs improve air-sealing, compared with the PVC cylindrical cuffs [21]. However, no significant difference was found between conical versus cylindrical polyurethane cuffs. A recent animal study evaluated the impact of PVC cuff shape on fluid leakage, using methylene blue as a marker for leakage. The authors concluded that leakage was significantly reduced in animals intubated with conical-cuffed tubes, compared with those intubated with cylindrical-cuffed tubes [23].

D’Haese et al. performed a randomized controlled study to evaluate the impact of conical cuff shape, compared with barrel cuff shape, on microaspiration of blue dye in 60 patients scheduled for lumbar surgery [24]. They reported that conical cuff shape was associated with reduced leakage of dye diagnosed using fiberoptic bronchoscopy. A recent multicenter randomized controlled study evaluated the impact of polyurethane and/or conical cuffs on tracheal colonization [25]. A total of 621 patients with an expected duration of mechanical ventilation longer than 2 days were included with cuffs composed of cylindrical PVC (n = 148), cylindrical polyurethane (n = 143), conical PVC (n = 150), or conical polyurethane (n = 162). No significant difference was found regarding the incidence of tracheal colonization or VAP between the different study groups. However, tracheobronchial colonization is probably not a good marker for microaspiration because antibiotic treatment might influence the rate of colonization. Whereas tracheobronchial colonization mainly results from aspiration of endogenous bacteria, contamination by exogenous bacteria is still possible [26, 27]. Several studies have shown that exogenous contamination could result from contaminated aerosols, tracheal suctioning or flexible bronchoscopy. Therefore, no definite conclusion could be drawn based on the results of the TOP-cuff trial.

### Study aim

The aim of this study is to determine the impact of a PVC conical-cuffed tracheal tube, compared with a PVC standard (barrel)-cuffed tracheal tube on abundant microaspiration of gastric contents in patients with a predicted duration of mechanical ventilation of at least 48 h. Secondary objectives include the impact of a conical-shaped tracheal cuff on microaspiration of oropharyngeal secretions, tracheobronchial colonization, VAP, and ventilator-associated event (VAE) incidence.

## Methods/Design

### Design

BEST CUFF is a multicenter, cluster randomized crossover controlled and open-label trial performed in patients receiving mechanical ventilation in the ICU. Because tracheal intubation is an urgent procedure in ICU patients, the randomization was performed on the participating ICUs, and not on the patients. These ICUs were randomized into two balanced groups, according to an intervention sequence. Using this design, half of ICUs are randomized to use a PVC conical cuff (Fig. 1) in the first 1-month period and a PVC standard cuff (Fig. 2) in the second 1-month period. The other half of the ICUs will use the two interventions in the reverse sequence.

**Fig. 1 Fig1:**
[figure not shown]
Conical tracheal cuff

**Fig. 2 Fig2:**
[figure not shown]
Standard tracheal cuff

Each ICU recruits distinct subjects during the repeated 2-month periods using the assigned intervention sequence, meaning that each intervention sequence started must be completed (Fig. 3).

**Fig. 3 Fig3:**
[figure not shown]
Randomization in participating intensive care units (ICUs). CC, conical cuff; SC, standard cuff

### Ethical aspects

The study protocol and patients (or next of kin) information documents were approved by the Ethical Committee, and Institutional Review Board of the Lille University Hospital (Comité de Protection des Personnes Nord-Ouest, approved 2 July 2013, registration 2013 A00534 41).

Complete and fair information is provided to the patient or to his representative. An informed written consent is obtained before enrollment. When consent is given by proxies, the patient is informed as soon as possible, and his written consent is obtained.

### Participating units

This study is currently conducted in ten French ICUs, including three located in university hospitals and seven in general hospitals.

### Study population

Inclusion criteria are age ≥18 years, intubation in the ICU with the study tracheal tube, an expected duration of mechanical ventilation of at least 48 h after inclusion. Exclusion criteria are age <18 years, pregnancy, patient or proxy refusal, contraindication for enteral feeding, intubation for >72 h at screening for eligibility in the trial, tracheostomy at ICU admission, previous enrollment in this study, or the inclusion in another study that may interfere with this trial.

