### Study protocol

Inclusions are performed 24 h/24 h, every weekday. After inclusion, tracheal aspirates are collected for 48 h to measure pepsin and amylase. When informed consent is obtained <12 h after intubation, tracheal aspirates collection is started at least 12 h after intubation (Fig. 4). All tracheal aspirates are stored at -20 °C in each hospital’s laboratory, and subsequently sent to the central laboratory at the Lille University Hospital, where all measurements of pepsin and amylase are blindly performed. Quantitative measurement of pepsin is performed by an ELISA technique, and salivary amylase activity is calculated by the difference between total and pancreatic amylase activity. The volume required to perform this analysis is 1 to 2 ml in each tracheal aspirate.

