### Data collections

At the time of inclusion, the following baseline characteristics are recorded: age, sex, height, body weight, date of hospital admission, date of ICU admission, patient location before ICU admission (home, hospital for >24 h), date of intubation and mechanical ventilation, preexisting comorbidities (diabetes and COPD, chronic restrictive respiratory failure, chronic heart failure, cirrhosis Child B or C, chronic renal failure, esogastroduodenal reflux, immunosuppression), McCabe score, Simplified Acute Physiology Score II, SOFA score, and reason for the ICU admission.

At the time of randomization, the following characteristics are recorded: SOFA score, duration of enteral feeding before randomization, nasal or oral position of the tracheal tube, cuff shape, and tube size.

During the 48 h following randomization, the variables listed below are recorded: ventilatory mode, mean PEEP, mean airway pressure, mean peak pressure, mean cuff pressure, highest FiO_2_, nitric monoxide use, aerosols, vasopressor support, enteral feeding volume, gastric residual volume, stress ulcer prophylaxis, use of prokinetic agents, vomiting, sedation, neuromuscular blockers, Glasgow Coma Score, mean head of bed elevation, prone position, patient mobilization (on chair), patient mobilization outside ICU room, accidental extubation, reintubation, and death.

Until day 28 or until ICU discharge, the following variables are being collected: sedation, transfusion, tracheotomy, extubation failure, accidental extubation, reintubation, shock, transport outside the ICU, mean head of bed elevation, use of proton pump inhibitors, ICU-acquired infection other than VAP (bacteremia, ventilator-associated tracheobronchitis, intravascular catheter-related infection, urinary tract infection, soft tissue infection, and others), duration of antibiotic treatment, duration of mechanical ventilation, length of ICU stay, death, data related to VAE, pepsin and alpha-amylase levels, VAP, and tracheobronchial colonization (Table 1).

**Table 1 Tab1:** Study flowchart follow-up

	Inclusion	H12 to H72	Until Day 28 or ICU discharge	Suspected VAP
Eligibility : check inclusion and exclusion criteria	X			
Randomization	X			
Quantitative TA culture	X		two times a week	X
Pepsin and amylase measurement in all TA for 48 h		X		
Clinical and radiological signs of VAP			X	
Quantitative TA culture or BAL				X
Clinical data			X	

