### Blinding

Blinding of physicians, nurses and patients is not feasible in this study. However, pepsin and amylase measurements are performed blindly. VAP diagnosis will be confirmed by at least two independent blinded physicians.

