#### Primary endpoint

The proportion of patients with abundant microaspiration will be compared between the two group using a generalized linear mixed model including group as fixed effect, and center and center*time period as the random effects. Missing data for the primary endpoint are being handled by multiple imputation using chained equations (m = 10 imputations using primary endpoint and patient’s characteristics at inclusion).

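### Recruiters know the cuff when they enrol, so case-mix could differ by cuff, and the primary model has group as its only fixed effect and would leave that difference in the estimate

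*Protocol article*

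**What the plan says.** **Allocation.** Under Design, "the randomization was performed on the participating ICUs, and not on the patients", and "half of ICUs are randomized to use a PVC conical cuff (Fig. 1) in the first 1-month period", with the other cuff in the next month. The other ICUs use the reverse order, and the 2-month sequences repeat.

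**Entry.** Under Study population, eligibility requires "intubation in the ICU with the study tracheal tube, an expected duration of mechanical ventilation of at least 48 h after inclusion". The exclusion "intubation for >72 h at screening for eligibility in the trial" leaves a window of up to 72 h between intubation and screening. Ethical aspects requires written consent from the patient or a representative before enrolment. Study protocol shows that this follows intubation: "When informed consent is obtained <12 h after intubation, tracheal aspirates collection is started at least 12 h after intubation".

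**Who enrols.** Trial conduct and data monitoring gives daily screening and inclusion to physicians, a research assistant, or both. Under Blinding, "Blinding of physicians, nurses and patients is not feasible in this study". No recruiter kept unaware of the cuff is described.

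**Analysis.** Under Statistical analysis, Primary endpoint, the comparison uses a "generalized linear mixed model including group as fixed effect, and center and center*time period as the random effects". Patient characteristics enter the primary analysis only through the multiple imputation of missing outcomes. Elsewhere they are compared between groups, with no link to adjustment. Data collections lists what is available, beginning "At the time of inclusion, the following baseline characteristics are recorded".

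**The concern.** Every step between allocation and inclusion is taken with the cuff known or knowable. These steps are judging that ventilation will last at least 48 h, choosing when within the 72 h to screen, and approaching the patient or family. If any of them runs differently in conical and standard months, the two groups differ in case-mix for reasons unrelated to the cuff's effect.

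The stated safeguards do not address this:

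- Intention-to-treat starts from the included patients. It cannot bring back those intubated in the period but never enrolled.
- Blinded pepsin and amylase assays and blinded confirmation of pneumonia protect measurement, not entry.
- The center random effect absorbs what is constant in an ICU. Each ICU-month has one cuff, so case-mix that varies systematically with the cuff is aligned with group. A zero-mean center-by-period effect adds variance but does not remove that shift.

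At stake is an unadjusted group effect that may be too large or too small, with no prespecified analysis in the article to correct even the measured part.

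**Working it through.** **1. The plan's own figures.** Inputs from Sample size: 50 % versus 30 %, two-sided alpha 5 %, power 80 %, ICC 0.035, 30 patients per ICU (15 per ICU and arm), 10 % without secretions.

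- Unclustered, unpooled variance: (1.960 + 0.842)² × (0.50×0.50 + 0.30×0.70) / 0.20² = 90.3 per group (plan: 90). The pooled-variance formula gives 93.
- Design effect: 1 + (15 − 1) × 0.035 = 1.49.
- Clustered: 91 × 1.49 = 136 and 93 × 1.49 = 139 (plan: 140, within 3 %).
- Attrition: 140 / 0.90 = 155.6, rounded up to 156 per group, 312 in total (plan: 312).

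The sample size reproduces and is not at issue. The effective size per group is 140 / 1.49 = 94, at which power is 80.4 %.

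**2. How much an imbalance could shift the estimate (assumed).** The documents give no figure for selection. Suppose a binary risk factor with odds ratio OR, present in 50 % of the standard-cuff group, where overall risk is 50 %, and no true cuff effect. The risks without and with the factor are then r0 = 1/(1 + √OR) and r1 = 1 − r0. The spurious risk difference is (prevalence difference) × (r1 − r0).

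| OR | r1 − r0 | Prevalence 50 % vs 40 % | Prevalence 50 % vs 30 % |
|---|---|---|---|
| 2 | 0.172 | 1.7 points (9 % of 20) | 3.4 points (17 %) |
| 3 | 0.268 | 2.7 points (13 %) | 5.4 points (27 %) |
| 4 | 0.333 | 3.3 points (17 %) | 6.7 points (33 %) |

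**3. Effect on error rates (assumed shifts s).** With 94 per group and no true effect, the two-sided rejection rate is Φ((s − 1.96·SE0)/SE1) + Φ((−s − 1.96·SE0)/SE1). SE0 is the pooled and SE1 the unpooled standard error for 50 % versus 50 % − s. If the shift instead opposes a true fall from 50 % to 30 %, power is that for 50 % versus 30 % + s.

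| Shift | False-positive rate | Power if opposed |
|---|---|---|
| 0 | 5 % | 80 % |
| 2 points | 5.9 % | 71 % |
| 5 points | 10.5 % | 55 % |
| 8 points | 19.5 % | 38 % |
| 10 points | 28.0 % | 28 % |

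Shifts of 8 and 10 points exceed anything in the first table and would need stronger or multiple imbalances.

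**4. Room for covariates.** Expected events under the planned rates: 280 × (0.50 + 0.30)/2 = 112. With four covariates plus group, that is 112 / 5 = 22 events per term.

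**The case against.** **The crossover.** Every ICU uses both cuffs, and any sequence begun must be completed, so stable ICU differences are balanced by design. This stands. A reader might infer that ten ICUs make chance imbalance likely; that reasoning belongs to a parallel cluster trial and carries little weight here. What remains is case-mix that moves with the cuff within an ICU.

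**No selection is shown.** Screening is daily, inclusion runs round the clock, and the urgency of intubation is a stated reason for randomising ICUs. This also stands. A reader might infer that the estimate will be biased, but the article supports only that it could be.

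**An unadjusted model is legitimate, and a detailed analysis plan is announced.** Both are true, and an adjusted sensitivity analysis could appear there. However, the article already fixes the primary model's fixed effect, random effects and imputation. The point concerns that stated choice, not an absent detail.

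**Adjustment can itself go wrong.** A reader might conclude that every recorded prognostic variable should be added, including time from intubation to inclusion, duration of enteral feeding before inclusion, and nasal or oral route. The documents do not support that. These are determined at or after placement of a known cuff, partly during the 72 h window, so adjusting for them need not reduce bias. Data collections also lists a date of intubation, not an hour.

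**Covariates do not repair recruitment.** Correct: they remove only the measured part.

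**Conclusion.** The point holds as a possible and uncorrected source of bias, worth a cheap change to the primary model. Recruiters know the cuff, entry follows intubation and involves judgement and consent, and nothing in the primary model separates a cuff effect from cuff-dependent case-mix within an ICU. The documents do not show that selection occurred, nor its direction or size.

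All magnitudes are illustrative. Under the assumed imbalances the shift is 1.7 to 6.7 points. A 5-point shift would take the false-positive rate from 5 % to 10.5 %, or power from 80 % to 55 % if it opposed the planned effect. These figures rest on the assumed prevalences and odds ratios and on the plan's own ICC of 0.035.

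**What to change.** In Statistical analysis, Primary endpoint:

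1. Add as fixed effects a short, prespecified list of characteristics that Data collections already records at inclusion and that the cuff cannot plausibly affect, for example age, esogastroduodenal reflux, diabetes and SAPS II. Reflux and diabetes connect to the reflux and hyperglycemia named among the risk factors in the Background. Age and SAPS II are general prognostic markers, and the article does not say how strongly they predict pepsin.
2. Leave time from intubation to inclusion, feeding duration before inclusion and tube route out of the primary model.
3. Keep the unadjusted model as a sensitivity analysis.
4. Report a standardised risk difference beside the conditional odds ratio.
5. Define *group* as the cuff allocated to the ICU on the date of the patient's first intubation. This settles patients intubated late in one month and included in the next. It is also needed because Data collections and Table 1 refer to randomization at patient level, although no patient is randomised.
6. State that adjustment removes only the measured part of any selection.

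**Cost.** A paragraph of analysis text and slightly more programming, with no new data. The odds ratio becomes conditional, which item 4 offsets. Trial status reports enrolment still open (201 included by March 2015), and the analysis plan is due before database lock, so on the article's own timetable the change can still be prespecified.
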